# A 21-Day School-Based Toothbrushing Intervention in Children Aged 6 to 9 Years in Indonesia and Nigeria: Protocol for a Two-Arm Superiority Randomized Controlled Trial

**DOI:** 10.2196/14156

**Published:** 2020-02-21

**Keywords:** school children, oral health, OHIs, DMFT, school program, knowledge transfer, behavior change

## Abstract

**Background:**

The World Health Organization reports that dental cavities affect 60% to 90% of children globally. FDI World Dental Federation and Unilever Oral Care have developed public health programs to improve brushing habits over their 12-year partnership. The last of these (phase III) named Brush Day & Night aimed to educate children on brushing twice daily with a fluoride toothpaste and gave useful information for a new project, phase IV. The 21-day Brush Day & Night program is an intense education activity designed to establish the habit of brushing day and night with a fluoride toothpaste. The program involves daily brushing instruction and includes free toothpaste and toothbrushes.

**Objective:**

The main objective of the study is to evaluate the impact of a 21-day school program on children’s oral health. As a secondary objective, we aim to evaluate the impact on the knowledge, behavior, toothbrushing habits, and quality of life in school children aged 6 to 9 years after a 21-day school program and compare with baseline and a control group as measured by the self-reported questionnaires issued to children (in particular, the self-reported brushing frequency and positive responses on fluoridated toothpaste use). The enduring nature of the program will be determined by the inclusion of 8- and 24-week time points.

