### Study Objectives

The main objective of the study is to evaluate the impact of a 21-day school program on children’s oral health. The primary objective is to evaluate the impact on knowledge, behavior, and toothbrushing habits in school children after a 21-day school program and compare with baseline and control group. Subsequent objectives will examine the impact on oral health, durability of the intervention, and any wider benefits on parent/carer and child well-being. The specifics of the objectives are outlined in Textbox 1.

Study objectives.Primary: measure the impact on knowledge, behavior, and toothbrushing habits in school children after a 21-day school program and compare with baseline and control groupSecondary: measure the impact on oral health via plaque levels at baseline and after a 21-day school program with children and compare with children in their control groupTertiary: evaluate the longer term impact of the 21-day program on knowledge, behavior, and oral health in children after a period of 8 weeks and 24 weeks (ie, approximately 7 months in total)Quaternary: provide evidence that the 21-day school program is effective in getting parents and carers to also improve their brushing habits and to brush day and nightQuinary: measure the change in quality of life, well-being, and social measures of school children after a 21-day oral health program

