### Selection of Schools

This is a cluster randomization trial with schools being the clusters, randomized to intervention or control groups. Schools need to be matched in terms of setting (city, suburb, rural) and socioeconomic status. The sample size calculation determined the number of schools that would be required to detect a difference between the test and control groups. The response of interest is an improvement in brushing behavior.

For Nigeria, it is assumed that 30% of the children are already brushing twice a day [6]. The trial is designed to detect a minimum 35% difference in the number of children brushing day and night at day 22 between the intervention group and the control group. It is assumed that the control group will see a 20% increase in proportion of children brushing twice a day due to the free toothpaste and toothbrushes they are given (Hawthorne effect). The interclass correlation has been set low at 0.05 and 0.10 (ie, low interpupil correlation) as we do not expect the children to influence each other in their brushing behavior because brushing will be carried out at home.

For Indonesia, it is assumed that 84% of the children are already brushing twice a day [6]. The trial is designed to detect a minimum 30% difference in the number of children brushing day and night at day 22 between the intervention and control group. It is assumed that the control group will have 40% of children brushing twice per day as a result of the Hawthorne effect. Again, the interclass correlation has been set at 0.05.

Therefore, for both Nigeria and Indonesia, the target number of schools is 20 (10 intervention and 10 control schools) calculated using power 80% and a significance level of .05. This number of clusters should also be sufficient to detect a difference of 0.5 in the OHI-S (plaque) at the same power and significance level. About 30 children in each class, in each grade, are anticipated, and for each child, the participation of a parent completing the questionnaires at each time point will be requested.

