### Study End Points

#### Assessment of Behavioral Change Impact

The objective of this study is to evaluate the impact of educational school programs in improving the oral health of local communities. The primary objective of the study analysis will be to measure the impact on knowledge, behavior, and toothbrushing habits in school children in Indonesia and Nigeria after a 21-day school program. This will be evaluated using three questions (specifically questions on behavior and knowledge) from the children’s questionnaire at all evaluation points (T0, T0+21, T1, T2). Improvement in knowledge and behavior will be calculated based on the percentage of positive change. Positive change is considered when a child selects the correct answers of twice daily brushing with a fluoride toothpaste.

The secondary objective employs the use of the OHI-S to assess plaque levels. More frequent brushing will result in lower plaque levels compared with baseline and compared with control groups. Plaque levels will be used to validate reported brushing frequency with assessments timed to align with questionnaire completion (how well are the children retaining and acting on the information/motivation delivered by the 21-day intervention?). To evaluate the longer term impact of the 21-day program on knowledge/behavior and oral health in children after periods of 8 weeks and 24 weeks, the children in the test group should report higher levels of brushing frequency and reduced plaque levels compared with children in the control group. To provide evidence that the 21-day school program is effective in getting parents and carers to also improve their brushing habits and to brush day and night, parents’ own brushing frequency, use of fluoride toothpaste, amount of toothpaste, and toothbrushes purchased should increase when compared with baseline and compared with parents in the control group. To measure the change in quality of life, well-being, and social measures of school children after a 21-day oral health program, children may report less dental discomfort/pain and need to take fewer days off school as a result. Additionally, at baseline (T0) and T2, all children will be scored for their caries prevalence using the DMFT index. No direct conclusions on the caries can be made but it is important descriptive information that is often not available in these two countries and could serve further research.

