Primary: measure the impact on knowledge/behavior and toothbrushing habits in school children after a 21-day school program and compare with baseline and a control group	Child questionnaire: reported brushing frequency, knowledge of the need to brush twice a day, reported use of fluoride toothpaste	within-group analysis: T0+21 vs T0; between-group analysis: T0, T0+21	Immersion in a structured 21-day school program will inform children of the importance of twice a day brushing with a fluoridated toothpaste and motivate improved brushing frequency.
Secondary: measure the impact on oral health via plaque levels in school children after a 21-day school program and compare with baseline and a control group	Child clinical observation: plaque levels (OHI-S^a^) will be used to validate reported brushing frequency with assessments timed to align with questionnaire completion (how well are the children retaining and acting on the information/motivation delivered by the 21-day intervention?)	within-group analysis: T0+21 vs T0; between-group analysis: T0, T0+21	More frequent brushing will result in lower plaque levels compared with baseline and compared with their control group.
Tertiary: evaluate the longer term impact of the 21-day program on knowledge/behavior and oral health in children after a period of 8 weeks (T1) and 24 weeks (T2) or approximately 7 months total	Child questionnaire: reported brushing frequency at T1 and T2; knowledge of the need to brush twice a day and reported use of fluoride toothpaste at T1 and T2; and OHI-S at T1 and T2 compared with baseline, after 21 days, and with control group	within-group analysis: T2 vs T0, T0+21, and T1 vs T0, T0+21; between-group analysis: T0, T0+21, T1, T2	Children in the intervention group will report higher levels of brushing frequency and reduced plaque levels compared with the children in the control group. This can be attributed to the 21-day intervention.

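### The abstract and the body rank oral health and brushing behaviour in opposite order, and the primary objective is not tied to one outcome and visit

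*Protocol article*

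**What the plan says.** **Abstract, Objective.** Oral health is the main objective. Behaviour is ranked below it: "As a secondary objective, we aim to evaluate the impact on the knowledge, behavior, toothbrushing habits, and quality of life in school children".

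**Introduction, Study Objectives.** The text opens with "The main objective of the study is to evaluate the impact of a 21-day school program on" children's oral health, and the next sentence reads "The primary objective is to evaluate the impact on knowledge, behavior, and toothbrushing habits in school children". Textbox 1 then lists knowledge, behaviour and habits as primary, plaque as secondary, the 8- and 24-week follow-up as tertiary, and quality of life as quinary.

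**Study End Points, Assessment of Behavioral Change Impact.** The primary objective is evaluated with three questions from the children's "questionnaire at all evaluation points (T0, T0+21, T1, T2"). Plaque comes next: "The secondary objective employs the use of the OHI-S to assess plaque levels".

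**Study End Points, Questionnaires.** Eight main questions are said to address the primary objective.

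**Statistical Analysis, Table 2.** The primary objective has three child-reported variables: "reported brushing frequency, knowledge of the need to brush twice a day, reported use of fluoride toothpaste". They are compared within and between groups at T0 and T0+21 only. T1 and T2 belong to the tertiary objective.

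**Selection of Schools (sample size).** "The response of interest is an improvement in brushing behavior". The calculation concerns twice-daily brushing at day 22, intervention against control, in Nigeria and Indonesia separately. The same section adds that the number of clusters should also suffice for a 0.5 difference in OHI-S.

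**The concern.** A superiority trial needs one agreed answer to the question of which result decides it. Here the abstract and the body give opposite answers on the outcome domain. Within the body, the sections differ on the visits and on the number of items that serve the primary objective.

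The practical risk is a split result. If reported brushing improves and plaque does not, the body supports calling the trial positive, and the abstract supports saying that the main objective was missed. If plaque improves and reported brushing does not, the roles swap. Either account could cite the published text. The two domains also differ in kind: one is the child's own report, the other a dental examination, and children and teachers in the intervention schools know that they had the programme. The choice between them is therefore not cosmetic.

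**Working it through.** **1. The sections side by side**

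| Section | Ranked first | Rank of the other domain | Visits for the first-ranked objective |
|---|---|---|---|
| Abstract, Objective | Oral health | Behaviour: secondary | Not tied to a visit |
| Study Objectives, opening | Oral health (*main*), then behaviour (*primary*) | – | After 21 days |
| Textbox 1 | Behaviour | Plaque: secondary | After 21 days |
| Assessment of Behavioral Change Impact | Behaviour | Plaque: secondary | T0, T0+21, T1, T2 |
| Table 2 | Behaviour | Plaque: secondary | T0, T0+21 |
| Selection of Schools | Twice-daily brushing | OHI-S also said to be powered | Day 22 |

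The first row cannot be reconciled with Textbox 1, the end-point section or Table 2. Quality of life also moves, from secondary in the abstract to quinary in the body. The visit sets in the end-point section and Table 2 differ by T1 and T2. The number of primary items is three in the end-point section and in Table 2, eight in the Questionnaires section and one in the sample size.

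**2. The plan's own figure**

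The plan gives no error rate for a set of tests, only a significance level of .05, 80% power and 20 schools per country. I tried to reproduce the 20 schools, reading the differences as percentage points, two-sided, with design effect 1 + (m − 1) × ICC, m = 30 and ICC = 0.05:

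- Design effect: 1 + 29 × 0.05 = 2.45.
- Indonesia, 40% v 70%: 42 children per arm unclustered; 42 × 2.45 / 30 = 3.4, so 4 schools per arm.
- Nigeria, 50% v 85%: 27 per arm unclustered; 27 × 2.45 / 30 = 2.2, so 3 schools per arm.

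The stated 10 per arm is not reproduced on this reading. An unstated allowance for attrition, matching or OHI-S could explain the excess. This has no bearing on the present point. The section matters here only because it shows which outcome, visit and contrast the trial was sized on.

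**3. What three unranked primaries could cost**

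Inputs: three variables (Table 2), two countries sized separately (Selection of Schools) and 5% per test. Assumptions: one between-arm test per variable at T0+21, and success declared if any one test is significant. With k independent tests, the chance of at least one false positive is 1 − 0.95^k.

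- One country, k = 3: 1 − 0.95³ = 1 − 0.857 = 0.143.
- Both countries, k = 6: 1 − 0.95⁶ = 1 − 0.735 = 0.265.

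The three items come from the same child and are probably positively correlated. At the other extreme, with perfect correlation within a country, the figures are 5% per country and 1 − 0.95² = 0.0975 across both. The range is thus 5% to 14% per country and about 10% to 26% across both.

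**The case against.** **The body has a consistent order.** Textbox 1, the end-point section and Table 2 all put behaviour first and plaque second, and the Statistical Analysis section says that the five outcome measures were prioritised. The end-point section also separates a broad aim about oral health from the primary objective of the analysis, so *main* in Study Objectives may mean an overarching goal. This stands for the body and makes Study Objectives clumsy more than contradictory. It does not rescue the abstract, which expressly labels behaviour secondary.

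**The plan does point to one result.** A reader might infer that nothing in it identifies a deciding result. That goes too far: the sample-size section fixes an outcome, a day and a contrast. But it never calls this the primary outcome, and Table 2 gives it no precedence over the other two variables.

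**There may be a single responder outcome.** The end-point section defines positive change as giving the correct answers on brushing twice daily with fluoride toothpaste. This can be read as one outcome built from three questions, with one test per country. That reading is possible and would bring the error rate to the lower end of the range above. Table 2 lists three variables, so the text does not settle it.

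**Stronger readings that the document does not support:**

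- *The trial has no multiplicity control.* Such rules are commonly left to a statistical analysis plan, which is not shown. Their absence from the article is not a finding.
- *The false-positive rate is about 60%.* This needs 18 independent tests (three variables, three post-baseline visits, two countries), hence T1 and T2 as primary. Table 2 places them under the tertiary objective, and only the loose phrase in the end-point section supports counting them.
- *The primary was chosen after results were seen.* The article says that it was published retrospectively and that the first part of the study ended in 2018. That makes documentation necessary; it shows nothing about how the choice was made.

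**Conclusion.** The point holds. The abstract contradicts Textbox 1, the end-point section and Table 2 on whether oral health or behaviour ranks first. The end-point section and Table 2 contradict each other on the visits for the primary objective. Table 2's three unranked variables do not match the single variable behind the sample size. These are conflicts in the stated text and do not depend on any calculation.

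The main consequence is that either reported brushing or plaque could be presented as the primary result. The secondary consequence is an illustrative false-positive chance of up to about 14% per country and about 26% across both. These figures assume independent or positively correlated items, each Table 2 variable tested once at 5% at T0+21, and any one significant test counted as success.

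**What to change.** 1. Declare one primary outcome: the between-arm difference in the proportion of children reporting twice-daily brushing at T0+21, in each country. This is the quantity already powered, taking day 22 and T0+21 as the same visit; say so, and name the question that defines it.
2. Make knowledge, fluoride toothpaste use and OHI-S at T0+21 secondary. Keep T1 and T2 tertiary, as in Table 2.
3. Align the abstract objective, the main-objective sentence in Study Objectives, Textbox 1, the end-point and Questionnaires sections, and Table 2. State that the between-group comparison decides and that within-group change is supportive.
4. State how the countries combine. Choose separate claims per country, one claim if either succeeds (Holm across the two: smaller *P* value against .025, then the other against .05), or one claim only if both succeed (no adjustment).
5. Record when the choice was fixed relative to access to outcome data.

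**Cost.** Mostly wording, plus a dated record of the decision, which matters because data collection was well advanced when the protocol was published. Knowledge and fluoride toothpaste use lose primary status. The country rule has a power cost: Holm makes the first test stricter than the .05 used in the sample size. Requiring both countries gives 0.80 × 0.80 = 64% joint power if each has exactly the planned 80%.

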**Methods:**

The study is a 2-arm superiority randomized controlled trial. Clusters in this study are infant and junior schools in Indonesia and Nigeria. The study aims to recruit 20 schools with children aged 6 to 9 years in each country. At baseline, children in both intervention and control schools will answer a questionnaire and have their clinical oral health assessed using the Simplified Oral Hygiene Index (OHI) and Decayed Missing and Filled Teeth index. Children in the intervention schools will then take part in a structured 21-day Brush Day & Night intervention. Children in the control schools will be provided with free toothpaste and toothbrushes but will not receive the 21-day intervention. The questionnaires and OHI assessments are repeated after the 21-day program is completed and again 8 weeks later and 24 weeks later for all participating children. Parents/carers/guardians of all children will sign the informed consent and complete questionnaires on their own experience and attitudes toward oral health and toothbrushing routine at each of the four times points (baseline, 21 days, 8 weeks, and 24 weeks). The study will be conducted by the national dental associations of Indonesia and Nigeria and was approved by the ethics committees of both countries.

**Results:**

The study is ongoing. Recruitment of schools started in Indonesia in February 2018 and in Nigeria in April 2018 for the first part of the study, which concluded in Indonesia in September 2018 and in Nigeria in November 2018. The second part of the study (the second half of the schools) started in November 2018 in Indonesia and December 2018 in Nigeria.

**Conclusions:**

We expect to collect all the data during 2019 and publish findings from the study by March 2020.

**Trial Registration:**

ClinicalTrials.gov NCT04001296; https://tinyurl.com/selxraa

**International Registered Report Identifier (IRRID):**

DERR1-10.2196/14156

## Introduction

### Prior Work

The Brush Day & Night (BDN) program is the result of a 12-year partnership between FDI World Dental Federation (FDI) and Unilever. It is an intense education activity designed to establish the habit of brushing day and night with a fluoride toothpaste. The program involves daily brushing instruction and includes free toothpaste and toothbrushes (see Multimedia Appendix 1 for more information).

The program was designed based on the theories of behavior change. Behavior change interventions and the formation of health promoting habits is thoroughly reviewed by Lally et al [1] and specifically in the context of interventions to improve tooth brushing by Claessen et al [2]. This and other research was crystallized into the Unilever 5 levers of change model [3], which is the foundation for the design of this particular intervention. The first step of the model is to identify barriers, triggers, and motivators to adopting a new behavior. Those insights are considered in designing a new behavioral intervention in 5 steps:

Make it understoodMake it easyMake it desirableMake it rewardingMake it a habit

This is a 21-day intervention, a duration chosen to reflect past research [4] that repetition of between 12 and 15 times is necessary to make a habit change, and 21 calendar days is 15 school days. The choice of schools within which to implement the program was influenced by the work of Pine et al [5] that states schools can be an optimum place for behavior change interventions where both parents and teachers may be involved in the intervention. The duration of 21 days was also chosen to avoid the program becoming overly onerous for the schools and teachers implementing the program.

Previous work has shown that the 21-day BDN program is effective in improving children’s toothbrushing knowledge and habits [6]. A study conducted in 10 countries with 7991 children aged between 2 and 12 years revealed that 25% more of the school children brushed their teeth twice a day at the close of the 21-day intervention. The program was found to be more effective among the 7 to 9 year age group.

### Rationale for the Study

The importance of preventing oral diseases to achieve good oral and general health is well known [7]. Regular twice-daily toothbrushing with a fluoride toothpaste is widely recommended for all age groups [8,9] and is effective in improving gingival health and preventing caries. It has been demonstrated that the successful adoption of good brushing habits in childhood can be effective in reducing dental caries risk for the longer term [10].

The 21-day BDN school program is a behavioral change intervention targeting primary school age children [6]. It is an immersive program designed to be delivered by dentists, dental nurses, or teachers at schools. This new study using the 21-day BDN school program aims to build on the previous results [6], with a new design. The previous study used nonprobabilistic convenience sampling with an intervention group only. Additionally, due to differences in evaluation time points which varied between 6 to 12 months, no quantitative conclusions could be drawn from the plaque index score. The study power and robustness of the methodology were cited as necessary improvements in a future investigation.

